### Data and safety monitoring

Regular monitoring will be conducted for quality control. Monitoring confirms whether the practical research-related data are correct compared with the source document as well as whether the research follows the approved protocol.

Adverse events indicate undesirable and unintentional signs, symptoms, or diseases that appear after the practical experiment, and they do not have to be causally related to the treatment. Safety will be evaluated based on the frequency, severity, and symptoms of the adverse event.

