Aside from the aforementioned systematic reviews, three recently conducted randomized controlled trials used a non-meridian point group as a control group. In two of these trials, the treatment group showed a marked improvement compared with the control group [12,13], but no significant difference was observed in one study [14]. There has been no proven placebo for acupuncture. The non-meridian point groups in the aforementioned studies are clearly considered not to be physiologically inert. These studies may therefore have had limitations in separating the specific effects of acupuncture [15].

This study was planned so as to use two forms of acupuncture; the first form, body acupuncture, indicates acupuncture that is applied to the whole body, in comparison with microsystem acupuncture that is applied to the specific local areas such as scalp acupuncture and auricular acupuncture. Acupuncture has a history that is at least 2,000 years old and has been used widely in China, Korea, and Japan [16-18]; the second form, Sa-am acupuncture, is traditional Korean acupuncture, which was developed in the latter part of the Joseon Dynasty. Sa-am acupuncture is a school of acupuncture initiated by Sa-am, which is characterized by applying the five-phase theory and the mother–child reinforcement–reduction principle to the selection of points and needling manipulation [12,16]. The control group is the usual care group, and we will measure the overall effects of acupuncture.

The aim of this study is to provide grounds for the effectiveness and safety of acupuncture by comparing the two acupuncture treatment groups and the control group.

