### Blinding

This is an unblinded study.

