### Intervention

Treatment groups will receive acupuncture treatment a total of 10 times for 4 weeks, and the control group will continue receiving their usual care. Meridian points that were used in two pilot studies will be applied to the two treatment groups [12,18]. The practitioner who will be providing treatment is a doctor of Korean medicine with over 3 years of practical experience and will have one training session so that he/she will be able to treat accordingly. Disposable needles with a diameter of 0.25 mm and a length of 30 mm (Dongbang Acupuncture Incorporation, Gyeonggi-do, Korea) will be used.

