### Other assessment measures

The treatment expectancy of each subject [27], as well as whether or not the subject satisfies the diagnostic criteria for CFS [2,5], will also be assessed.

The detailed outcome assessment time points are provided in Table 1.

**Table 1 T1:** Schedule for treatment and outcome assessment

**Period**	**Screening**	**Treatment**										**Follow**-**up**	
Visit	1	2	3	4	5	6	7	8	9	10	11	12	13
Week		1~4										5	13
Informed consent	•												
Demographic characteristics	•												
Medical history	•												
Laboratory test, chest X-ray, electrocardiogram, pregnancy test	•												
Inclusion/exclusion criteria	•												
Numeric rating scale	•	○										•	•
Vital signs	•	•	○	○	○	○	○	○	○	○	○	•	•
Change of medical history		•	○	○	○	○	○	○	○	○	○	•	•
Random allocation		•											
Treatment expectancy questionnaire		•											
Chronic fatigue syndrome questionnaire		•											
Fatigue Severity Scale	•	○										•	•
A short form of Stress Response Inventory	•	○										•	•
Beck Depression Inventory	•	○										•	•
EuroQol-5 Dimension	•	○										•	•
Acupuncture treatment		○	○	○	○	○	○	○	○	○	○		
Safety assessment		•	○	○	○	○	○	○	○	○	○	•	•

•, all groups; ○, treatment groups.

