### Hypothesis and sample size

The following two hypotheses are related to the differences between the treatment groups and the control group:

$$H_{0}:\mu_{1}=\mu_{3,}\;\mu_{2}=\mu_{3}$$

$$H_{1}:\mu_{1}\neq \mu_{3}\;\mathrm{or}\;\mu_{2}\neq \mu_{3}$$

where μ_1_ is the FSS mean score for treatment group A, 5 weeks after random allocation; μ_2_ is the FSS mean score for treatment group B, 5 weeks after random allocation; and μ_3_ is the FSS mean score for control group, 5 weeks after random allocation.

Referring to the previous study [28], the researchers expect that the difference between treatment group A and the control group will be smaller than the difference between treatment group B and the control group. This study therefore calculated the sample size taking into consideration the difference between treatment group A and the control group while applying the Bonferroni method, which is conservative among multiple comparison methods.

In the present study, changes from baseline in FSS mean score in the control group were calculated under the assumption that they would approximate 5% of changes in FSS mean score for treatment group A. The final calculated difference in changes in FSS mean score between the two groups was 0.915 with a standard deviation of 1.1479 [12,29].

Using the mean comparison method, this study will use an α value of 5%, a power of 90%, and the two-sided test:

$$\begin{array}{ll} \;n & =\frac{2\times {\left(Z_{\alpha /4}+Z_{\beta }\right)}^{2}\times \sigma^{2}}{\delta^{2}}\\ & =\frac{2\times {\left(2.2414+1.282\right)}^{2}\times 1.1479^{2}}{0,915^{2}}=39.08\approx 40 \end{array}$$

When the same number of patients is allocated for treatment groups A and B and the control group, each group has 40 patients. Considering a 20% dropout rate, each group will require 50 initial participants.

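### Safety is assessed at nine visits between randomization and week 5 in the acupuncture groups and at none in controls, so comparing all recorded adverse event frequencies with control would rest on unequal ascertainment

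*Protocol article*

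**What the plan says.** All references are to the protocol article.

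- **Aim (Background).** The trial is meant to "provide grounds for the effectiveness and safety of acupuncture by comparing the two acupuncture treatment groups and the control group". The Abstract's Background describes the same three-group comparison for both effectiveness and safety.
- **Measure (Data and safety monitoring).** "Safety will be evaluated based on the frequency, severity, and symptoms of the adverse event". The definition of an adverse event is all-cause: "they do not have to be causally related to the treatment".
- **Schedule (Table 1, under Other assessment measures).** The row "Safety assessment" is empty at visit 1, has a filled dot at visit 2, open circles at visits 3 to 11, and filled dots at visits 12 and 13. The key for the two symbols reads "all groups; ○, treatment groups", the filled dot standing for the first and the open circle for the second.
- **Contact with participants (Intervention).** "Treatment groups will receive acupuncture treatment a total of 10 times for 4 weeks, and the control group will continue receiving their usual care".

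The row for change of medical history follows the same pattern from visit 2 onward. The article mentions no diary, telephone call or other contact with controls between visit 2 and week 5. It also does not limit the comparison with control to the visits that all groups share.

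**The concern.** An adverse event enters the data only if somebody asks about it or the participant volunteers it. During treatment, participants in groups A and B are assessed every few days. Controls go from the randomization visit to week 5 without a scheduled assessment. Because the definition is all-cause, everyday complaints such as a cold or a headache count in every arm, and these are the events most easily forgotten over several weeks.

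A table of all recorded events by arm would therefore mix two things: any real difference in risk, and the difference in how often participants were assessed. The expected direction is an excess in the acupuncture groups, which would make acupuncture look less safe relative to usual care than it is. What is at stake is the control comparison for safety, which is a stated aim. The primary outcome is not touched.

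**Working it through.** **1. Counting the schedule.** The article gives no total, so the counts are read from the safety row of Table 1 with its key.

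| Window | Groups A and B | Control |
|---|---|---|
| Visit 2 (randomization) | 1 | 1 |
| Visits 3 to 11 | 9 | 0 |
| Visit 12 (week 5) | 1 | 1 |
| Visit 13 (week 13) | 1 | 1 |
| All visits | 12 | 3 |
| After visit 2 | 12 − 1 = 11 | 3 − 1 = 2 |

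Visits 2 to 11 are the 10 acupuncture sessions, so the nine extra assessments are those attached to the second to tenth sessions.

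**2. Where the arms differ.** The whole imbalance lies between visit 2 and visit 12. From visit 12 to visit 13 no group has a visit, so the interval is 13 − 5 = 8 weeks in every arm.

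**3. Whether it can matter.** Three statements have to be read together: the aim compares acupuncture with control on safety, the measure includes frequency, and events count regardless of cause. Under these, an event in a control during weeks 1 to 4 is as relevant as one in group A or B, but its first scheduled opportunity to be recorded after randomization is week 5.

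**4. Possible size.** The article gives neither an event rate nor a recall rate, so what follows is an illustration under assumptions:
- the true risk *p* of a short-lived event during treatment is equal in all arms;
- every such event is recorded in groups A and B;
- controls report a fraction *f* of theirs at week 5.

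The recorded risks are then *p* and *f × p*, and the apparent risk ratio is *p / (f × p) = 1 / f*, whatever *p* is.

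The last column takes *p* = 20% (assumed) and the planned group size ("Considering a 20% dropout rate, each group will require 50 initial participants"), so that 50 × 0.20 = 10 participants have an event in each group.

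| *f* | Apparent risk ratio, 1 / *f* | Recorded participants with an event, acupuncture group vs control |
|---|---|---|
| 1.0 | 1.00 | 10 vs 10 |
| 0.8 | 1.25 | 10 vs 8 |
| 0.6 | 1.67 | 10 vs 6 |
| 0.4 | 2.50 | 10 vs 4 |

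**5. Group A against group B.** Both follow the same 12-assessment schedule, so this comparison is free of the problem.

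**The case against.** The strongest reply is that the article specifies no adverse event test. Statistical methods applies analysis of covariance to the primary and secondary outcomes, and safety is not among them. The sentence on evaluating safety compares nothing in itself. How events are tabulated is commonly left to a full protocol or analysis plan, which is not shown. This stands to the extent that a reader might infer that a biased safety test has been planned, and the article does not say so. What it does contain is a comparative safety aim and a printed schedule that gives controls no assessment between randomization and week 5. If an analysis plan already limits the control comparison to the common visits, the analysis side of the point is met.

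Three further inferences are tempting and not supported:
- **That controls face longer recall throughout.** The 8 weeks before visit 13 are the same for everyone. Only the treatment period differs.
- **That 12 against 3 means a three- or fourfold excess of events.** Events arise over time at risk, not per question. Suppose each assessment has the same assumed chance *q* of eliciting an event. The ratio [1 − (1 − *q*)^12] / [1 − (1 − *q*)^3] is 3.2 at *q* = 5% and 1.9 at *q* = 20%, and it tends to 4 as *q* falls. That model has no basis in the article and builds the excess in, because it treats a gap of a few days like one of several weeks.
- **That all events are affected alike.** If the week 5 assessment covers the whole interval since visit 2, serious and lasting events should surface in every arm. The shortfall would mainly concern brief, minor ones. The article does not say what interval week 5 covers.

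It is also fair to say that safety checks at needling sessions are ordinary practice and worth keeping, and that the bias runs against a favourable safety claim.

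**Conclusion.** The point holds in a limited form. Table 1 gives 12 scheduled safety assessments to acupuncture participants and 3 to controls, with 9 against 0 between the randomization visit and week 5. Given an all-cause definition and an aim that compares safety with control, a comparison of all recorded frequencies would tend to show more brief, minor events in groups A and B at equal true risk.

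The counts are exact. The size of the distortion is not known: it is nil with complete control recall at week 5, and a risk ratio of 1.25 to 2.5 if controls report 80% down to 40% of treatment-period events. Those fractions, and full capture in the acupuncture groups, are assumptions. The finding does not bear on the efficacy analyses or on group A against group B. It is a cheap improvement worth making, not a flaw that undermines the trial.

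**What to change.** State in the analysis plan, and reflect in the case report form:

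1. The safety comparison with control uses only the common week 5 and week 13 assessments.
2. At both, all three groups get the same question, covering the whole interval since the previous common assessment (from visit 2 at week 5; from week 5 at week 13).
3. Events recorded at visits 3 to 11 are reported separately for groups A and B, for example per session, without comparison to control.

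**Cost.** The change is a matter of wording and one shared question at two existing visits; no visit is added and the session checks stay. The article reports that recruitment is under way, so participants already past week 5 would not have been asked the new question.

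**Downsides.** The comparative table relies on longer recall and will miss some minor events in every arm. Some bias may also remain, since participants asked repeatedly at sessions may remember more at week 5 than controls do. The report should say so.

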## Discussion

This study is designed as a pragmatic clinical trial to more closely reflect the effects of everyday treatment of acupuncture [31]. The results of this study are expected to provide evidence, with high external validity, for the effectiveness and safety of two common forms of acupuncture treatment on chronic fatigue patients.

In this study, the meridian points that will be used on the participants in treatment group A are intended to relieve the mind, clear the spirit, tranquilize the body to free it from tension, and regulate the functions of internal organs [18].

Sa-am acupuncture treatment is largely divided into three types: fixed pattern, transformed pattern and experienced prescription. In this study, the two latter types were applied to the participants in the treatment group B [12,32].

## Trial status

The present study is currently recruiting participants.

## Abbreviations

CFS: Chronic fatigue syndrome; FSS: Fatigue Severity Scale; ICF: Idiopathic chronic fatigue.
